### Study design

Specific Aim 1: observational cross-sectional study

Specific Aim 2: randomized clinical trial

### Procedures

*Summary:* This study will be conducted in two phases. Initially, 20 HIV-1 infected patients from each of several clinic sites will be screened by stool microscopy for the presence of helminth co-infection. These data will be used to determine the prevalence of infection at various sites and to compare baseline variables between groups as described above. These data will also help determine which study site will likely provide a population with sufficiently high prevalence in which to conduct the second phase of the study. This second phase will be a randomized double blind, placebo controlled clinical trial of anti-helminth treatment among HIV-1 and helminth infected adults. All patients will receive therapy for helminth infection either immediately or deferred (at twelve weeks post enrolment). As patients will be screened at enrolment for helminth infection, total prevalence will be calculated and determined for the entire screened population.

*Pilot study to identify optimal trial site:* Initially, we will conduct a pilot study to determine the prevalence of helminth co-infection in HIV-1 infected individuals in several clinic sites at different locations in or around Nairobi and some potentially in more rural sites elsewhere in Kenya. Twenty HIV-1 infected individuals will be enrolled at each clinic site and fresh stool obtained for microscopy. Individuals with helminth infections will either be offered enrolment in the treatment phase of the study described below (if proximate to the proposed site of the clinical trial study) or treated with open label albendazole 400 mg a day for three days and referred back to the clinic in which they receive regular care.

The study site that is the most feasible for the trial will be selected based on the data from the pilot study (specific aim 1) to be the base for larger scale screening to identify 200 HIV-1 infected helminth co-infected individuals. Specific factors that will be considered for site selection include helminth prevalence and ability to recruit HIV-1 infected helminth co-infected individuals. Depending on helminth prevalence this may require screening ~600 to 2000 individuals (10% to 30% estimated helminth prevalence).

### Clinical Trial:

a) Screening for trial eligibility: At the selected clinical trial study site, HIV-1 infected individuals who meet inclusion and exclusion criteria will be informed about screening for stool helminths. A physical examination will be conducted on all prospective clients, and those found to have clinical pallor, or signs and symptoms of tuberculosis, malaria or malignancy will be excluded from the study and referred for appropriate medical management. Individuals with CD4 counts >250 cells/mm^3 will be eligible for study screening following written informed consent for study screening. For those individuals without available CD4 count data, patients will be screened if there is no evidence of WHO Stage II-IV disease. Patients who are subsequently found to have CD4 counts less than 250 cells/mm^3 will be referred for further HIV care at the referring clinic. The individual clinic sites will be notified of all CD4 count results within 14 days of testing. Baseline demographic and socio-economic data will be collected from these patients using standardized questionnaires. Stool samples will be collected and evaluated for ova and parasites. Participants who are found to have positive stool parasite examinations will be

informed about the clinical trial and those who consent to participate will be enrolled in the treatment phase of the study. Those who are found to be infected with helminths but who decline to participate in the treatment phase will be treated at no charge with a three day course of 400mg/day of albendazole by the study investigators. Those who are found to have negative stool specimens will not continue to the treatment phase. After screening exit (either due to lack of helminths or declining to participate), individuals will be referred back to the clinic in which they receive their usual care.

b) *Clinical trial*: HIV-1 infected helminth co-infected individuals who elect to participate in the randomized clinical trial will be enrolled following written informed consent. Those patients who are enrolled in the treatment phase will have blood collected for baseline plasma HIV-1 RNA levels and CD4 cells. Computer-generated random number allocation will be used to assign treatment group. The pharmacy at the clinic will be responsible for the determination of randomization group and distribution of albendazole and placebo. The pharmacy will also be responsible for maintaining records regarding treatment group. Treatment will be provided in the form of three 400 mg pills of albendazole or a three placebo pills identical in appearance (to be taken one pill per day for each of three consecutive days). Both placebo and albendazole will be provided in an identical appearing envelope. Treatment arms will consist of either initial therapy with albendazole (400 mg a day for three days) or an initial three days of placebo pills. All patients will be required to visit the clinic eight weeks after enrollment. At this twelve-week visit, stool samples will again be collected for evaluation of helminth infection. Plasma CD4 count and HIV-1 RNA level measurements will be repeated at this twelve-week visit. All patients who received placebo initially as well as all patients with evidence of helminth infection will be treated with open-label albendazole therapy regardless of initial treatment arm.

At enrollment and the twelve-week visit, lymphocytes will also be isolated from serum samples for assessment of immune activation markers. Genital HIV-1 RNA levels will be compared in 100 individuals randomized to immediate versus deferred antihelminthics at baseline and at the 3-month visit (prior to receiving deferred therapy). This will provide data quantifying the potential effect of anti-helminthic treatment on genital HIV-1 RNA. Consenting adults will have genital swabs collected (semen or cervical/vaginal) and placed in freezing media prior to cryopreservation and transport to Fred Hutchinson Cancer Research Center for HIV-1 RNA assays.

Patients who do not follow-up as directed will be contacted by the administrative support team at their homes in order to determine the reason for each loss to follow-up. Any adverse events during the treatment period will be reported and managed accordingly at the treatment clinic.

### Laboratory

*CD4 measurement* will be assessed by FACSCalibur in Nairobi, Kenya.

*Stool microscopy* will be performed by technicians with training and certification in the differentiation and quantification of stool helminth species. Testing will be done using conventional microscopic techniques.

*HIV-1 RNA levels* will be quantified at the [name]'s laboratory at Fred Hutchinson Cancer Research Center in Seattle. Below is an explanation of the reasons for preference of this laboratory site:

1. Research collaborations have involved long-standing relationships with the University of Nairobi, KEMRI, and KNH, and University of Washington and the Fred Hutchinson Cancer Research Center. This collaboration has conducted studies in HIV infected individuals in Kenya for many years. HIV-1 RNA assays for these studies have been done at the laboratory of [name] in Seattle, USA. Dr.

[name] has made significant efforts to transfer technology for HIV-1 DNA filter paper assays and HIV-1 RNA assays for research studies. We are optimistic that DNA filter paper assays and potentially HIV-1 resistance assays will be conducted in Nairobi within 2 years.

2. Over the past many years, [name] laboratory has taken care to delineate subtype-related issues to optimize measurement of HIV-1 RNA in Kenya with a non-commercial Gen-Probe TMA (transcription-mediated assay) specifically tailored for subtypes A, D, and C from Kenyan isolates. Thus, it is useful to correlate the proposed study to other large-scale studies in Nairobi conducted by our research team.
3. Available funding for this study will not be sufficient to measure viral RNA in even 60 individuals at 2 time-points if these measurements were done locally (cost per assay in Nairobi ~4-5 times the cost at [name] laboratory). Under the current budget constraints we would likely be limited to a small subgroup analysis of 30 patients.

Given the improved design of the study with an increased sample size including 200 individuals, measuring HIV-1 RNA in all participants would significantly strengthen the study and increase the potential that significant effects on viral decline would be found.

*Immune activation markers* will be assessed using flow cytometry available at the University of Nairobi. Antibodies to relevant cell surface molecules, in combination with either anti-CD4 or -CD8 will be used for a measure of global T cell activation. Numbers of CD4+ and CD8+ T cells expressing the nuclear antigen, Ki67, will be used as a marker for ex vivo proliferating cells. Naïve and memory subsets will be determined from CD4+ and CD8+ T cell populations by staining patterns for differentiation markers CD45 and CD27: CD45RA+ CD27+ (naïve), CD45RA CD27+ (memory), CD45RA+CD27 (effector) and CD45RA CD27 (memory/effector), CD-38, and HLA-DR. HIV-1 specific responses (CD8 interferon gamma and IL-2) will be determined using Elispot and intracellular cytokine staining (ICS) in a subset of 20 individuals using cryopreserved PBMC specimens. Flow-Jo software will be utilized to quantify results.

### *Data Management*

*Data Entry and Storage:* All data will be collected on preprinted forms that are able to be scanned directly or data entered into a software data management program (Teleform SPSS or ACCESS). Data will be collected at enrollment and at each follow up visit on these forms. Following collection, the data forms will be scanned into the database as described above. Original data forms will be stored in the study offices with access restricted to study investigators. Following completion of all data collection, the data forms will be archived. At 1-year following completion of the study, identifiers will be removed from the data. Data will be the property of KEMRI and the University of Washington.

*Data verification:* A data clerk from KEMRI will be employed to hand verify that all data is completed accurately and that the computerized scanned data is comparable to the paper forms. Data will be cleaned by the Fellow Investigator and the data clerk and at that time a second verification of accuracy will be performed.

*Data Analysis:*

**Aim 1:** Prevalence of helminth co-infection will be determined in the total screened population by individual, by clinic and by cohort. To determine correlates of helminth co-infection, mean CD4 count, age and log10 RNA levels will be compared in individuals with and without helminth co-infections using t-tests. Dichotomous variables (socio-demographic) will be compared with Chi square tests in individuals with and without helminth co-infection. Similar analyses will be conducted to determine correlates of re-infection and eradication.

**Aim 2:** All analyses will be intent-to-treat. To assess the success of randomization we will compare baseline characteristics between the 2 randomization groups. To determine the effect of antihelminth treatment on disease progression markers, we will compare month one measurements of mean CD4 count, log10 plasma HIV-1 RNA, and percentage of cells with specified immune activation markers in the 2 study arms using t-tests or non-parametric testing. In addition, prevalence of helminth co-infection will be compared in the 2 study arms using Chi-square tests. To determine the effect of antihelminth treatment on infectivity, we will compare enrollment measurements of mean genital HIV-1 RNA levels with the 12 week follow up measurements.

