**Abstract:**

Most HIV-1 infected individuals in areas of high seroprevalence live in crowded urban settings. These conditions are associated with repeated helminth infections, which may alter immune function increasing the susceptibility and severity of other infections in these individuals. Prior observational studies have shown that in HIV-1 infected individuals, helminth infections are associated with immune activation and increased HIV-1 RNA levels. It is important to determine whether treating helminth co-infection in patients with HIV-1 will slow disease progression or reduce transmission.

We plan to determine the prevalence of helminth infection in HIV infected adults, characterize the short-term effect of antihelminth therapy on HIV-1 disease progression and immune activation markers, and examine co-factors for helminth infection, such as CD4 count, viral load, age, gender and duration of time spent in an urban setting. In addition, we will conduct a randomized clinical trial to determine the effect of helminth eradication on markers of immune activation and HIV-1 disease progression and transmissibility. The study will be conducted in a group of HIV-1 infected individuals who do not yet meet criteria for HAART. Identifying inexpensive and practical methods to delay HIV-1 progression offers tremendous public health benefits. At the present time, highly active antiretroviral therapy is being rapidly scaled up in resource poor settings. The demand for these drugs currently far outweighs the capacity for such services to be provided in many regions. For the millions of people affected and infected by HIV-1 in resource poor settings, delaying immunosuppression for months to years could allow important developments in infrastructure that would permit the maximum number of individuals to benefit from highly active antiretroviral therapy. In addition, it is important to identify inexpensive and effective methods to reduce HIV-1 transmission.

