### **Specific Objectives:**

1. To determine prevalence and correlates of helminth co-infection in HIV-1 infected individuals in various clinics in or around Nairobi, Kenya. Baseline demographic, socio-economic and geographic data such as age, gender, income, education, occupation and place of residence will be collected and compared to determine what factors influence the prevalence of helminth infection in patients with HIV-1.
2. To determine if treatment of intestinal helminths in HIV-1 infected adults can delay disease progression, as measured by CD4 counts and HIV-1 RNA viral loads.
3. To determine if treatment of intestinal helminths in HIV-1 infected adults can reduce shedding of genital HIV-1 and impact transmission.

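### Aim 1 sets out to find which factors influence helminth prevalence, but its unadjusted two-group tests can show only marginal association

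*Protocol*

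**What the plan says.** Specific Objectives, item 1, opens with "To determine prevalence and correlates of helminth co-infection in HIV-1 infected individuals in various clinics in or around Nairobi, Kenya". It continues "Baseline demographic, socio-economic and geographic data such as age, gender, income, education, occupation and place of residence will be collected" and gives the purpose: the data are to be "compared to determine what factors influence the prevalence of helminth infection in patients with HIV-1". The Abstract widens the list; the study will "examine co-factors for helminth infection, such as CD4 count, viral load, age, gender and duration of time spent in an urban setting". Under Study design the aim is labelled "Specific Aim 1: observational cross-sectional study".

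The method is in the Data Analysis part of Data Management, under Aim 1. For continuous variables, "mean CD4 count, age and log 10 RNA levels will be compared in individuals with and without helminth co-infections using t-tests". For the others, "Dichotomous variables (socio-demographic) will be compared with Chi square tests in individuals with and without helminth co-infection". The paragraph ends: "Similar analyses will be conducted to determine correlates of re-infection and eradication".

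Prevalence is to be reported by clinic. For the factor comparisons themselves the protocol names no stratification, adjustment or model, and it does not limit the results to unadjusted description.

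**The concern.** The objective speaks of influence, and the design does nothing to balance the candidate factors. Income, education, occupation and place of residence can be expected to go together, and age and gender may be related to all of them. A two-group test on any one then also picks up the others. Where several clinics contribute people, it also picks up differences between clinics in both prevalence and social mix.

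At stake is the reading of Aim 1. A factor with no association of its own may be reported as influencing prevalence, and the size of a real one may be misstated. The same applies to the CD4 comparison, because a difference by infection status may partly reflect age, gender or social position. By the protocol's own wording the problem carries over to the analyses of re-infection and eradication.

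**Working it through.** **Inputs from the protocol.** Procedures asks for 200 co-infected individuals and expects to screen about 600 to 2000, at a prevalence of 10% to 30%. Sample Size uses alpha 0.05 for the trial; I assume two-sided 0.05 for Aim 1, where none is stated.

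**The plan's own figure.** Number to screen = 200 / prevalence.
- At 10%: 200/0.10 = 2000, as stated.
- At 30%: 200/0.30 = 667, against about 600. Screening 600 would imply 200/600 = 33%. This is loose rounding and does not matter here.
- At 20%, a midpoint I add: 200/0.20 = 1000.

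**Assumptions not in the protocol.** Two binary factors, each present in 50% of people. Factor A multiplies prevalence by R. Factor B has no association of its own but has correlation φ with A. R and φ are varied because the protocol gives neither.

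**Formulas.** With overall prevalence p:
- without A, p0 = 2p/(1+R); with A, p1 = R·p0
- prevalence with B = (1+φ)/2·p1 + (1−φ)/2·p0; without B, the two weights are exchanged
- the difference between the B groups is therefore φ(p1−p0)
- standard error = √[2p(1−p)/(N/2)]
- rejection rate ≈ P(Z > 1.96 − difference/SE), the opposite tail being negligible except when the difference is small

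**One case in full:** N = 667, p = 0.30, R = 2, φ = 0.3.
- p0 = 0.60/3 = 0.20; p1 = 0.40
- with B: 0.65×0.40 + 0.35×0.20 = 0.33; without B: 0.27; difference 0.06
- SE = √(0.42/333.5) = 0.0355; ratio 0.06/0.0355 = 1.69
- P(Z > 1.96 − 1.69) = P(Z > 0.27) ≈ 0.39

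**Rate at which the chi-square test on B is significant:**

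| R | φ | 667 at 30% | 1000 at 20% | 2000 at 10% |
|---|---|---|---|---|
| 1.25 | 0.3 | 9% | 8% | 8% |
| 1.5 | 0.2 | 10% | 10% | 9% |
| 1.5 | 0.3 | 17% | 16% | 15% |
| 1.5 | 0.4 | 27% | 24% | 22% |
| 2 | 0.2 | 20% | 18% | 17% |
| 2 | 0.3 | 39% | 35% | 32% |
| 2 | 0.4 | 62% | 56% | 51% |

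A simulation of these cells with 40,000 runs each agrees to within one percentage point.

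**Wider range, and the effect of adjustment.** A separate simulation (1000 runs per cell) used odds ratios of 1.5, 2 and 3 for the true factor and φ of 0.2, 0.3 and 0.5. For 600 to 2000 screened, the unadjusted test on the null factor was significant in about 5% of runs at the weak end (odds ratio 1.5, φ 0.2, N = 600) and 93% at the strong end (odds ratio 3, φ 0.5, N = 2000). With the true factor also in a logistic model, the rate was about 4% to 6% throughout.

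**Clinic.** Take two groups of clinics with prevalence 10% and 30%, and a factor unrelated to infection within each group. If its frequency is 40% in one group and 60% in the other, the pooled chi-square test is significant in 9% of runs with 100 and 700 people, 25% with 300 and 300, and 62% with 1000 and 1000. At 30% against 70% the rates are 23%, 67% and 99%. A Mantel-Haenszel test stratified by clinic group stays at about 5% to 6%. The unequal split is closest to the protocol's scheme of 20 people at each pilot clinic followed by large-scale screening at one selected site.

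**The case against.** **A marginal association is a correlate.** Objective 1 opens with correlates, and the analysis paragraph runs its tests to find correlates. In the model above, infection really does differ between people with and without factor B, so the tabulated rates are power to detect a true marginal difference. This stands. A reader might infer that Objective 1 cannot be answered at all, but prevalence and marginal correlates are both delivered. The conflict is only with the word influence, which the protocol itself uses.

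**The rates are assumed.** Also true. A reader might infer that spurious factors will often be declared. The protocol gives no correlations and no effect sizes, so it supports only that this can happen, and will happen often if factors are moderately to strongly related.

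**Adjustment could be left to a statistical analysis plan.** The absence of a model would not be a finding by itself. Here, though, the protocol is not silent. It names the tests by which correlates are to be determined, and those tests do not match the stated purpose.

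**Adjustment is not a cure-all.** The return to 5% assumes that the true factor is known, measured without error and in the model. Fitting income, education and occupation together may also remove effects that act through one another. Nor should CD4 simply be added to the list: Introduction and Background and the Hypothesis treat CD4 count and viral load as things helminth infection may change, and conditioning on a consequence of infection can bias the other coefficients. This limits what any model can claim and shapes the fix, but it does not make the unadjusted tests adequate for the stated purpose.

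**The trial's hypothesis is not touched.** A reader might infer that a confounded CD4 contrast in Aim 1 weakens the trial result. It does not, because that hypothesis concerns treatment against no treatment and is tested in the randomized Aim 2.

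**Conclusion.** The point holds as a mismatch between the stated purpose of Aim 1 and its named analysis. Unadjusted t-tests and chi-square tests identify marginal correlates; they do not show which of several related factors, or clinic, carries the association.

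The size is conditional on effect sizes and correlations that I have assumed. The chance that a factor with no association of its own reaches significance runs from near 5% with weak relations, through about 9% to 17% (prevalence ratio 1.5, correlation 0.2 to 0.3) and 17% to 62% (ratio 2, correlation 0.2 to 0.4), to higher values with stronger confounding. This affects a secondary, observational aim. It is worth correcting because the correction is cheap and uses data already planned.

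**What to change.** In Data Analysis, Aim 1:
- Keep the two-group tests, labelled as description.
- State that factors will be judged from one prespecified multivariable model of infection status: logistic regression, or Poisson regression with robust errors if prevalence ratios are wanted.
- Include age, gender, income, education, occupation, residence or urban duration, and clinic where several sites contribute. Report adjusted estimates with 95% confidence intervals.
- Do not enter CD4 or viral load as predictors alongside the social factors. Compare each by infection status in a separate analysis adjusted for the demographic factors and clinic.
- Count parameters rather than variables when fixing the model. With 200 infected people, 20 per parameter allows 200/20 = 10, and a factor with several categories uses several.

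The cost is a few sentences and a short analysis of data already to be collected. Intervals will be slightly wider for strongly related factors.

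If the investigators prefer not to model, Specific Objective 1 should claim unadjusted associations only and drop the reference to influence. Either change removes the mismatch.

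### The Aim 2 between-arm comparison is set at month one, when no CD4, plasma HIV-1 RNA or activation-marker sample is scheduled, and the one follow-up visit itself carries two week labels

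*Protocol*

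**What the plan says.** The Aim 2 paragraph (Protocol, Data Management, Data Analysis) gives the between-arm analysis of disease progression: "we will compare month one measurements of mean CD4 count", with log10 plasma HIV-1 RNA and the percentage of cells carrying activation markers, by t-tests or non-parametric tests.

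The sampling is set out in Protocol, Clinical Trial, item b. At entry, participants "will have blood collected for baseline plasma HIV-1 RNA levels and CD4 cells". For follow-up, "Plasma CD4 count and HIV-1 RNA level measurements will be repeated at this twelve-week visit". For the activation markers, "At enrollment and the twelve-week visit, lymphocytes will also be isolated from serum samples for assessment of immune activation markers".

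The same item introduces the follow-up visit with "All patients will be required to visit the clinic eight weeks after enrollment", and the next sentence refers to it as the twelve-week visit.

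**The concern.** The analysis text and the procedures give different times for the same outcomes. Month one is an explicit time point and it matches no scheduled sample. It also sits in the only place where the protocol fixes when the arms are compared on CD4, plasma RNA and activation markers. The Sample Size section powers the trial on a CD4 difference of 40 cells/mm³ but gives no time for that difference, so it cannot settle the question.

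What is at stake is whether the protocol states, before data are seen, how long after treatment the effect is measured. At present it does not do so consistently. An analysis plan that followed the Aim 2 sentence literally would have nothing to analyse, and one that used the follow-up visit would depart from the protocol's stated time.

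**Working it through.** No arithmetic is needed beyond counting. The check sets every stated time for the Aim 2 outcomes side by side.

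**Time named in the analysis (Data Analysis, Aim 2)**
- CD4, log10 plasma RNA, activation markers: month one.
- Genital HIV-1 RNA: the enrolment values are compared as "mean genital HIV-1 RNA levels with the 12 week follow up measurements".
- Helminth prevalence by arm: no time given.

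**Time of collection (Clinical Trial, item b)**
- CD4 and plasma RNA: enrolment and the twelve-week visit.
- Lymphocytes for activation markers: enrolment and the twelve-week visit.
- Stool: the same twelve-week visit.
- Genital RNA, in a subset of 100: baseline and the 3-month visit, before deferred therapy.
- The required clinic visit: first placed at eight weeks, then called the twelve-week visit.

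**Supporting statements elsewhere**
- The Procedures summary and the Risks text under Ethical Considerations both put deferred treatment at twelve weeks.
- The Laboratory section's cost argument is framed around the budget to "measure viral RNA in even 60 individuals at 2 time-points", which fits one baseline and one follow-up assay.

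**Count**
- Planned participants: 100 per arm × 2 arms = 200.
- Scheduled post-baseline times for CD4, plasma RNA and activation markers: 1.
- Scheduled month-one measurements of these markers: 0, so 0 of 200 participants.
- Follow-up times written for these outcomes, taking month one as about 4 weeks: 4 (analysis text), 8 and 12 (procedures), so 3 candidates for one measurement.

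The analysis time matches neither label in the procedures. Correcting the Aim 2 sentence alone would point it at a visit whose own timing is stated in two ways.

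**The case against.** The strongest reply is that this is a drafting slip with little effect on inference. These markers have one scheduled post-baseline measurement, so the comparison can only use that sample. That stands, and it removes several stronger conclusions a reader might draw:

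- *That the analyst could pick a favourable time afterwards.* With one scheduled follow-up sample there is little to pick from. Neither bias nor an inflated type I error follows from this sentence.
- *That a site would add a four-week blood draw.* Nothing in the procedures suggests it, and the two-time-point cost argument points away from it.
- *That four weeks would capture one third of the intended exposure contrast.* Four weeks is one third of the twelve-week deferral (4/12), but treatment is a three-day course at the start. The documents give no basis for scaling the treatment contrast with elapsed time.
- *That Aim 2 contradicts itself because genital RNA is analysed at 12 weeks.* A separate outcome, measured in a subset, may have its own time. The contradiction is between the analysis text and the procedures.

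Two further replies are fair but do not change the result. The Inclusion Criteria and the Data Entry text speak of follow-up visits in the plural and there is no visit table, so the absence of a month-one visit is an inference; still, no part of the protocol places a draw of these markers then. The protocol also labels no analysis as primary. It is, however, the only between-arm analysis given for the markers of Specific Objective 2, and CD4 is the only sample-size variable.

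Deferring to a statistical analysis plan does not answer the point: the protocol has stated a time, and it does not fit the protocol's own sampling.

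**Conclusion.** The point holds as an error in the stated time. The only specified between-arm analysis of the disease-progression markers is set at month one, where 0 of 200 participants have a scheduled measurement, and the visit that does supply the data is labelled both eight and twelve weeks. Three candidate times are therefore in the text.

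A reader might go further and infer that the comparison cannot be made at all, or that its result would be biased. The documents do not support that: one follow-up sample is planned for every participant, and the analysis can be run on it once the wording is corrected.

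The conclusion assumes that month one means about four weeks and that the procedures list all draws of these markers. It takes no position on which visit week is right.

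**What to change.** Make three changes in one edit.

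1. In Data Analysis, Aim 2, replace the reference to month one by the measurements from the single follow-up visit at which CD4, plasma RNA and lymphocytes are drawn, and state that these are taken before deferred treatment.
2. In Clinical Trial, item b, reconcile the eight-week and twelve-week descriptions of that visit. The investigators must say which was intended.
3. Use one label for this visit throughout Aim 2: CD4, plasma RNA, activation markers, stool helminths and genital RNA.

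The cost is a few lines of wording in two sections. No new data, assay or visit is needed.

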### Sample Size

Sample size determination – Assuming a power of 80% and alpha of 0.05, we have calculated that 100 individuals would be needed in each arm to detect a difference in CD4 count of 40 cells/mm^3 following anti-helminth therapy (SD of 200 cells/mm^3).

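### Aim 2 compares follow-up values between arms without using the baseline of the same measure, which is collected; the test is valid but gives away precision

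*Protocol*

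**What the plan says.** Protocol, Data Management, Data Analysis, Aim 2: the arms are compared on follow-up mean CD4, log10 plasma HIV-1 RNA and "percentage of cells with specified immune activation markers in the 2 study arms using t-tests or non-parametric testing". The sentence labels these as month-one measurements. For these three outcomes, baseline data enter only through a comparison of baseline characteristics meant to show that randomization worked.

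Protocol, Clinical Trial, part b: "Those patients who are enrolled in the treatment phase will have blood collected for baseline plasma HIV-1 RNA levels and CD4 cells". For follow-up, "Plasma CD4 count and HIV-1 RNA level measurements will be repeated at this twelve-week visit". For the markers, "At enrollment and the twelve-week visit, lymphocytes will also be isolated from serum samples for assessment of immune activation markers". All three outcome families are therefore planned at both enrolment and follow-up.

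Protocol, Sample Size: "Assuming a power of 80% and alpha of 0.05", the protocol states that "100 individuals would be needed in each arm" "to detect a difference in CD4 count of 40 cells/mm"³, with "SD of 200 cells/mm"³. It does not say whether this is the SD of the CD4 value, of its change or of a residual. It mentions neither adjustment nor a correlation.

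**The concern.** When the same quantity is measured before and after randomized treatment, a two-sample test on the follow-up values alone leaves in the error term all the between-person variation that the baseline value could explain. A linear model with baseline as a covariate removes that part. The protocol pays for the baseline measurement and then leaves it out of the treatment comparison. This is a choice the protocol states, not a detail it is silent on.

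At stake is precision: wider confidence intervals and a lower chance of detecting the 40-cell difference for which the trial was sized. The Laboratory section argues for measuring RNA in all 200 participants so that an effect on viral decline is more likely to be found. A decline is measured from baseline, so an analysis that ignores baseline sits awkwardly with that aim.

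**Working it through.** **Inputs.** From Sample Size: difference 40, SD 200, 100 per arm, alpha 0.05, power 80%. Assumed: two-sided test (sidedness is not stated), SD 200 is the SD of the CD4 value, no dropout. The baseline-to-follow-up correlation r is not in the protocol and is shown as a range.

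**The protocol's own figure first.** n per arm = 2 × (1.960 + 0.842)² × 200² / 40² = 393, not 100 (310 if one-sided). With 100 per arm, SE = 200 × √(2/100) = 28.3 and 40/28.3 = 1.414, so power = Φ(1.414 − 1.960) = 29%. The stated 100 per arm does not follow from its inputs. That is a separate point; it matters here only because it sets the starting power.

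**With baseline adjustment.** Residual SD = 200 × √(1 − r²). SE = residual SD × √(2/100). Power by normal approximation = Φ(40/SE − 1.960). The exact column uses the noncentral t with 197 degrees of freedom.

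| r | residual SD | power, normal | power, exact t | n per arm for 80% |
|---|---|---|---|---|
| 0 (same SD as the planned test) | 200.0 | 29.3% | 29.1% | 393 |
| 0.3 | 190.8 | 31.7% | 31.4% | 358 |
| 0.5 | 173.2 | 37.2% | 36.9% | 295 |
| 0.7 | 142.8 | 50.8% | 50.4% | 201 |
| 0.8 | 120.0 | 65.4% | 65.0% | 142 |

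Reaching 80% with 100 per arm needs r of about 0.86.

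**Cost.** One degree of freedom (197 instead of 198). With r = 0 the exact power rounds to 29.1% either way.

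**Relative gain.** Adjustment multiplies the variance of the comparison by 1 − r². That equals enlarging the sample by 1/(1 − r²): 1/0.75 = 1.33 at r = 0.5, 1/0.51 = 1.96 at r = 0.7 and 1/0.36 = 2.78 at r = 0.8. This ratio does not depend on the SD; the absolute power figures do.

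**Change score for comparison.** SD of change = 200 × √(2(1 − r)): 200.0, 154.9 and 126.5 at r = 0.5, 0.7 and 0.8. Power is 29%, 45% and 61%. It gains nothing at r = 0.5 and is below ANCOVA at each of these values.

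**The case against.** The strongest reply is that nothing here is wrong. In a randomized two-arm trial a between-arm test of follow-up values holds its type I error and is unbiased. That stands: a reader might infer that the planned test is invalid, and the documents do not support that. Nor is chance baseline imbalance a second harm. Its standard error for CD4, 28.3 cells, is the same quantity as the SE of the unadjusted follow-up comparison if the SD is equal at both visits. It is already counted in the 29%.

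The size of the gain is also open. No correlation is given, and the CD4 entry criterion (above 250) restricts the baseline range and may lower it. At r = 0.3 the gain is about 2 percentage points, at r = 0.5 about 8. If 200 is an SD of change, the power series does not apply. No SD is given for RNA or the markers, so the series covers CD4 only.

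A reader might go further and say that CD4 and viral load differ between people far more than any twelve-week effect could, or that this is the largest free improvement available. The documents show neither. The Introduction and Background cites a viral-load contrast of 0.36 + 0.67 = 1.03 log10 between participants with and without documented clearance of helminths, and a CD4 difference of 279 − 192 = 87 cells after treatment. No alternative improvements have been compared.

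Finally, covariates and the rule for choosing between a t-test and a rank test are often left to a SAP. For the choice of test that is fair, and the open choice is not pressed here. For the covariate it carries less weight, because the protocol does name the analysis, and both of its options ignore baseline.

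**Conclusion.** The point holds as one of efficiency. The protocol fixes an unadjusted comparison for outcomes whose baseline it also collects. On the assumptions of a two-sided test, SD 200 for the CD4 value and no dropout, power for 40 cells is about 29% as planned and about 37%, 50% and 65% with adjustment at r = 0.5, 0.7 and 0.8. The direction is secure whenever r is more than trivially different from zero; the size is conditional on an r that the protocol does not give.

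It would be tempting to read adjustment as the remedy for the sample size. It is not: below r of about 0.86 the stated 80% is still missed, and the mismatch between 100 per arm and its own inputs must be dealt with separately.

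**What to change.** In Data Analysis, Aim 2, make the primary analysis a linear model (ANCOVA) of the follow-up value on arm and the baseline value of the same measure, for CD4, log10 plasma HIV-1 RNA and each activation marker. Report the adjusted difference between arms with its 95% CI. Keep a rank-based or unadjusted test as a named sensitivity analysis, which also settles which test is primary.

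In the same sentence, reconcile the month-one label with the visit described in Clinical Trial, part b. That section calls it the twelve-week visit but also places a visit eight weeks after enrolment. Until this is settled, the follow-up value in the model is not defined.

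In Sample Size, say what the SD of 200 refers to and, if adjustment is to be counted, which correlation is assumed.

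The adjustment needs no new visit, assay or participant: it is a change of analysis wording and costs one degree of freedom. Reconciling the visit is a further edit across sections.
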